### Follow up

After the 4-week treatment period, patients will be followed up for 8 weeks. The medical staff will follow up the participants via telephone. Each participant is contacted once every 2 weeks, keeping record of the medications and rehabilitation therapies. On the final week of the follow-up period (8 weeks post intervention), participants will be referred for clinical evaluation in order to assess their prognosis and disability condition.

### Outcome measures

In this study, primary outcomes will be measured at baseline and the end of every week from the 1st to the 4th week. Secondary outcomes will be measured at baseline and the end of the 4th week. During each treatment, adverse events and untoward effects will be assessed. After follow up (8 weeks), the prognosis and disability condition outcomes (GOS and Disability Rating Scale (DRS)) will also be evaluated. All outcome assessments will be independently performed by experienced and blinded assessors, the same one professional rehabilitation physician. A summary of all the measures in the trial is shown in Table 1.

### Primary outcomes

#### Glasgow Outcome Scale

The GOS is used to assess the recovery and outcome of patients with TBI. The severity of disability is divided into 5 levels according to indicators such as whether the patients can recover to undertake work, study, and self-care. The 5 levels are death, vegetative state, severe disability, moderate disability and good recovery.

### Secondary outcomes

#### Glasgow Coma Scale

The GCS was first introduced by Jones et al. in 1979 [29]. It is a brief scale with 15 points in total, divided into 3 items: Eye Opening Response (E), Verbal Response (V) and Motion Response (M).When the resulting GCS is between 13 and 15 points, and the duration time of coma after injury is shorter than 20 min, this means that the patient has light TBI; when the resulting GCS is between 9 and 12 points, and the duration time of coma after injury is between 20 min and 6 h, this means that the patient has moderate TBI; when the resulting GCS is between 6 and 8 points, and the duration time of coma after injury is longer 6 h, this means that the patient has severe TBI; and when the resulting GCS is between 3 and 5 points, this means that the patient has extremely severe TBI.

### Brainstem auditory evoked potential

The BAEP is sensitive in detecting brain stem auditory pathway lesions, and has been used for more than two decades. Many scholars use it to assess brain function in acute critical illness, and it has been widely used to evaluate the degree and prognosis of TBI [30, 31]. Greenberg first proposed the BAEP grading standard in 1977 [32]. Later, many scholars took this as the standard for clinical research and improvement; other new classification methods have also been proposed. At present, there are more than ten kinds of BAEP grading standards. The Hall grading standard [33] is one of the most detailed. It divides the abnormal BAEP condition into 4 levels: level 1 normal and level 2 mildly abnormal: I ~ V wave well-differentiated, but changeful in any of the following situations such as I, III, or (and) V wave PL extend, I ~ III,III ~ V or (and) I ~ V wave PL extend, III ~ V/I ~ III peak to peak latency phase ratio > 1, V/I amplitude ratio < 0.5; level 3: moderately abnormal: III and (or) V wavelength division poor, poor repeatability, or missing V wave; and level 4: severely abnormal: only the I-wave or both waves are absent.

### Upper sense evoked potential

The USEP is used to stimulate the upper skin or peripheral nerve. Firstly, the nerve impulses transmit to the spinal cord along the afferent neural pathway. Secondly, the nerve impulses transmit to the thalamus along the ascending sensory pathway of the spinal cord. Thirdly, the nerve impulses transmit to the cerebral cortex central posterior sensory area along thalamic central radiation. Finally, the corresponding contra hemisphere cortex of the stimulated upper skin can be activated [34]. Amantini [35] suggests that UESP has high accuracy in predicting the prognosis in DOC.

### EEG data

The EEG is an effective method to evaluate and predict brain function [36]. We will measure changes in participants’ brain function.

### Safety assessments

The medical staff will record adverse events (AEs) that occur at any time during treatment. When a serious AE occurs, the Ethics Committee of the First Affiliated Hospital of Nanchang University will determine whether the participant needs to be withdrawn from the study. We will treat AEs free of charge.

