## Method/design

### Study design

The clinical study is a prospective, randomized controlled trial designed with double-blinded assessments, and is being carried out in 80 patients hospitalized with DOC after TBI. All participants will be randomly allocated to the intervention group or control group in a 1:1 ratio. The control group will receive conventional rehabilitation combined with sham tDCS therapy, and the intervention group will receive conventional rehabilitation combined with active tDCS therapy. This trial will comprise a 4-week intervention and 8-week follow-up period. The relative primary outcome (Glasgow Outcome Scale (GOS)) will be measured at baseline and the end of every week from the first to the fourth week. The secondary outcomes (Glasgow Coma Scale (GCS), brainstem auditory evoked potential (BAEP), and upper sense evoked potential (USEP) will be measured and electroencephalogram (EEG)) performed at baseline and the end of the fourth week. During each treatment, adverse events, and untoward effects will be measured. The first affiliated Hospital of Nanchang University (NCU), which will undertake the study, is responsible for training rehabilitation therapists on standard operating procedure and supervising the progress of this trial in all clinical sites. In addition, the randomization and blinding will be performed by an independent statistician from the Center of Evidence Based Medicine, NCU. A flow diagram of this trial is presented in Fig. 1

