### Participants and recruitment

The participants will be recruited from the intensive care unit (ICU) and the neurologic intensive care unit (NICU) at the First Affiliated Hospital of Nanchang University. Our study will be advertised on the Internet homepage of First Affiliated Hospital of Nanchang University between December 2019 and December 2020. Posters will select the potential objects who perhaps meet the inclusion criteria by looking through patients’ medical histories via the Computerized Patient Record System (CPRS) and inform patients and their families about this trial is displayed in hospital via phone, or email. Interested families can contact the project leader further. After obtaining informed consent, the prospective participants are screened by a neurologist from the NICU at The First Affiliated Hospital of Nanchang University, according to the inclusion and exclusion criteria. Those who satisfy all criteria are eligible to participate. The eligible individuals are invited to participate in the trial and are directed to a diagnostic assessment by a neurologist, followed by rehabilitation assessments. Consent will be obtained for all study participants from their family members. Data on the design of the study are shown in Table 1.

**Table 1 Tab1:** Data on the design of the study

Point in time	Screening stage	Treatment period 1 (1 week)	Treatment period 2 (2 weeks)	Treatment period 3 (3 weeks)	Treatment period 4 (4 weeks)
Informed consent	X				
Inclusion and exclusion criteria	X				
Withdrawal, drop out and termination criteria		X	X	X	X
Basic information	X				
Past medical history	X				
Therapeutic parameter record		X	X	X	X
Glasgow Coma Scale (GCS)	X	X	X	X	X
Glasgow Outcome Scale (GOS)		X	X	X	X
EEG	X				X
Brainstem auditory evoked potential (BAEP)	X				X
Upper sense evoked potential (USEP)	X				X
Overall efficacy evaluation					X
Complications	X	X	X	X	X
Adverse events recorded	X	X	X	X	X

*EEG* electroencephalogram

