### Data collection and management

General baseline information will be collected about patients when they are sent to the hospital and will include the following: age, sex, nationality, education level, disease type, course of illness. Major indicators are assessed at the end of the 1st, 2nd, 3^rd^, and 4th week of treatment, including application of the GOS after 4 weeks of treatment, all secondary index evaluations: the BAEP, body feeling on USEP, and EEG data. For each treatment, safety is assessed in terms of adverse events and adverse reactions.

Outcomes will be assessed using the GOS at the end of 1st, 2nd, 3rd, and 4th week, and will be performed using the BAEP, USEP, and EEG at the end of the 4th week of treatment. Complications during follow up will also be assessed. If the patient is still in the hospital, the investigator may visit the patient on the ward to go through the evaluation. If the patient has been discharged, his or her legal representative will be told to come back in due time for assessment after leaving the hospital. If the patient does not arrive, the investigator will try to contact the patient or the family members by telephone. Other possible methods may also be used to explain the situation and complete the outcome assessment. If all attempts fail, no further contact will be made, and the patient will be recorded as lost to follow up.

All the data will be collected by independent investigators who are blind to the patient’s allocation. Each local study center will assign a specific investigator at the beginning of the trial. This investigator will be excluded throughout treatment of all the participants unless asked by clinicians to perform the assessment.

All variables specified in the protocol will be documented on standardized hard-copy case report forms (CRFs) in all participating centers. When the 8-week follow up is complete, data in the CRF of each patient will be validated for completeness, consistency, and plausibility, by an independent investigating physician in a local center. Then the CRF will be transmitted to the Center of Evidence Based Medicine, NCU, which will be responsible for the development of a central database, and data entry and storage. At the end of the trial, the database will be locked and sent to the study statistician for analysis based on a predetermined statistical analysis plan.

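### Adverse-event recording is tied to the 4 treatment weeks, so the planned between-arm comparison need not include events from the 8-week follow-up

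*Protocol article*

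**What the plan says.** The Background section lists evaluating the safety of tDCS in these patients as the second objective and gives it no time window. Study design sets the length of observation: "This trial will comprise a 4-week intervention and 8-week follow-up period".

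Safety data are described in several places:

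- **Safety assessments:** "The medical staff will record adverse events (AEs) that occur at any time during treatment".
- **Outcome measures:** "During each treatment, adverse events and untoward effects will be assessed". The Abstract and Study design say the same in similar terms.
- **Data collection and management:** "For each treatment, safety is assessed in terms of adverse events and adverse reactions". The same section later adds: "Complications during follow up will also be assessed".
- **Follow up:** "Each participant is contacted once every 2 weeks, keeping record of the medications and rehabilitation therapies". A clinical evaluation closes this period, 8 weeks after the intervention.
- **Outcome measures, on the end of follow-up:** "the prognosis and disability condition outcomes (GOS and Disability Rating Scale (DRS)) will also be evaluated".
- **Table 1:** the row "Adverse events recorded" is marked at screening and in each of the four treatment weeks. Complications have a row of their own. The table has no follow-up column.

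The Statistical analysis section names one safety comparison: adverse events are to be listed and tested with a chi-square or Fisher's exact test.

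**The concern.** The safety objective is open-ended, but the recording rule is not. Every sentence that names adverse events attaches them to treatment, and the description of the follow-up calls contains no safety item. The one safety comparison named in the article is of adverse events.

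Suppose a participant has a seizure or is readmitted in week 7. Under the text as it stands, no instruction has this recorded as an adverse event, and nothing brings it into the comparison between arms. It might be noted as a complication. But the article does not say what a complication is, whether it counts as an adverse event, or whether it is compared between arms.

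At stake is how far the safety statement reaches. The trial stays in contact with each participant for 12 weeks but could end up comparing adverse events over only the first four.

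**Working it through.** **Inputs**

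- Treatment: 4 weeks; follow-up: 8 weeks (Study design).
- Call interval: 2 weeks (Follow up).
- Participants: 80 (Study design).
- Adverse-event window: the treatment period. Some sentences could be read as covering only the individual sessions. The wider reading, all four weeks, is used here.

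The article states no figure for the share of time covered, so there is none to reproduce.

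**Share of time inside the window**

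- Weeks after randomisation: 4 + 8 = 12, taking treatment to start at randomisation.
- Share inside: 4 / 12 = 33.3%. Share outside: 8 / 12 = 66.7%.
- For 80 participants with no dropout: 80 × 4 = 320 of 80 × 12 = 960 patient-weeks.

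**Contacts already available outside the window**

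- Calls: 8 / 2 = about 4 per participant, plus the closing clinical evaluation.
- With adverse events recorded at these contacts, coverage becomes 12 / 12 = 100%.

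**The passages side by side**

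| Place | Weeks 1–4 | Weeks 5–12 |
|---|---|---|
| Safety assessments | adverse events | not mentioned |
| Outcome measures | adverse events | GOS and DRS at the end |
| Data collection and management | adverse events and reactions | complications |
| Follow up | not applicable | drug use, rehabilitation, closing evaluation |
| Table 1 | adverse events and complications, in separate rows | no column |
| Statistical analysis | adverse events compared, no window given | adverse events compared, no window given |

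The comparison has no time limit of its own, but it can only use what was recorded as an adverse event. Recording is stated for treatment only, so the inclusion of later events depends on whether complications count as adverse events. The article does not settle this. Because Table 1 gives the two separate rows, they cannot simply be assumed to be the same thing.

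**The case against.** Four arguments can be made on the other side.

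**Safety-type information is planned throughout.** Complications are assessed during follow-up, a clinical evaluation closes it, the GOS includes death as a level, and the DRS measures disability. Case report forms are validated only after the 8-week follow-up. This stands. A reader might infer that the safety objective is addressed on only a third of the observed time, and the documents do not support that. What they support is narrower: the stated adverse-event window covers a third. The GOS and DRS are planned as prognosis and disability outcomes and do not record discrete non-fatal events.

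**Table 1 proves little.** A reader might take its adverse-event and complications rows, which end at week 4, as evidence that recording stops there. The table has no follow-up column and also omits the GOS and DRS at the end of follow-up, so every row must end at week 4. This stands, and the point rests on the text instead.

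**The article condenses a fuller protocol, and a predetermined analysis plan is mentioned but not shown.** Definitions and call scripts may be found there, and the general rule for discrete measures could cover complication counts. It is therefore not established that complications go unanalysed. But the treatment window is stated, and stated repeatedly. It is not a detail the article merely leaves out.

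**An on-treatment window is a recognisable choice.** The only tDCS effects the Background lists are tingling, itching, burning and mild pain, which are effects of stimulation itself, and nothing in the article suggests delayed harm. This limits the likely consequence. It does not explain why contacts already planned should omit a safety question when the objective has no time limit.

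**Conclusion.** The point holds in a limited form. The text ties adverse-event recording to 4 of the 12 weeks after randomisation, and the link between follow-up complications and adverse events is left undefined. The named between-arm comparison therefore need not include events in weeks 5 to 12. This rests on reading the recording sentences as they stand; a fuller protocol could resolve it.

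A reader might go further and estimate how many participants per arm would have an unrecorded event. The documents do not support such a count. They give no event risk, and the result would turn on an assumed hazard over time: if harms cluster around stimulation, the number approaches zero. Such a count would also treat follow-up complications as not captured at all, contrary to the Data collection and management section. No effect on the direction or size of the between-arm comparison is shown either.

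This is an inexpensive improvement that serves a stated objective. It does not invalidate the safety assessment.

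**What to change.** Reconcile the Follow up, Outcome measures, Safety assessments, and Data collection and management sections with Table 1, so that all give the same rule:

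1. Record adverse and serious adverse events from the first treatment to the clinical evaluation 8 weeks after the intervention, asking about them at the 2-weekly calls and at that visit.
2. Define complications, and code those arising in follow-up on the same form as adverse events.
3. Add follow-up columns to Table 1 showing these assessments.
4. In Statistical analysis, report the adverse-event comparison twice: for the treatment period and for the whole 12 weeks. The tests already named can stay. Matching wording belongs in the Abstract and Study design.

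The cost is one extra question and form at contacts that already take place, slightly longer calls, more events to code, and a text revision. It should be in place before enrolment, which Trial status puts in December 2019, because events not collected at the time cannot be reliably reconstructed later.

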### Data collection and management

General baseline information will be collected about patients when they are sent to the hospital and will include the following: age, sex, nationality, education level, disease type, course of illness. Major indicators are assessed at the end of the 1st, 2nd, 3^rd^, and 4th week of treatment, including application of the GOS after 4 weeks of treatment, all secondary index evaluations: the BAEP, body feeling on USEP, and EEG data. For each treatment, safety is assessed in terms of adverse events and adverse reactions.

Outcomes will be assessed using the GOS at the end of 1st, 2nd, 3rd, and 4th week, and will be performed using the BAEP, USEP, and EEG at the end of the 4th week of treatment. Complications during follow up will also be assessed. If the patient is still in the hospital, the investigator may visit the patient on the ward to go through the evaluation. If the patient has been discharged, his or her legal representative will be told to come back in due time for assessment after leaving the hospital. If the patient does not arrive, the investigator will try to contact the patient or the family members by telephone. Other possible methods may also be used to explain the situation and complete the outcome assessment. If all attempts fail, no further contact will be made, and the patient will be recorded as lost to follow up.

All the data will be collected by independent investigators who are blind to the patient’s allocation. Each local study center will assign a specific investigator at the beginning of the trial. This investigator will be excluded throughout treatment of all the participants unless asked by clinicians to perform the assessment.

All variables specified in the protocol will be documented on standardized hard-copy case report forms (CRFs) in all participating centers. When the 8-week follow up is complete, data in the CRF of each patient will be validated for completeness, consistency, and plausibility, by an independent investigating physician in a local center. Then the CRF will be transmitted to the Center of Evidence Based Medicine, NCU, which will be responsible for the development of a central database, and data entry and storage. At the end of the trial, the database will be locked and sent to the study statistician for analysis based on a predetermined statistical analysis plan.

#### Data Safety and Monitoring Committee (DSMC)

The project will be monitored by the DSMC, initiated by the clinical trial center of The First Affiliated Hospital of Nanchang University, and composed of specialists in rehabilitation, ethics, statistics, and methodology. The DSMC will audit the study through regular interviews or telephone calls.

### Statistics methods

#### Statistical analysis

SPSS21.0 software will be used to analyze the test results. In the descriptive analysis of the sample, continuous variables will be expressed by mean and standard deviation for normally distributed data, and median and interquartile range for non-normally distributed data. Normally distributed data variables will be statistically compared between groups using the *t* test. Ordinal-level variables with a non-normal distribution will be statistically compared between groups using the Mann–Whitney *U* test. Measures with a discrete distribution will be expressed as percentages and analyzed using the chi-squared (χ2) or Fisher’s exact test as appropriate. A general linear model or logistic regression model will be applied to adjust for confounding influences if necessary.

We will compare baseline characteristics between groups using the *t* test or Mann–Whitney test for continuous variables and the Pearson chi-squared or Fisher’s exact test for categorical variables. If statistical significance appears, the inequality factors will be treated as confounding variables in the final efficacy analysis. For comparison of the primary or secondary outcomes between groups, the *t* test or non-parametric tests will be used to analyze continuous data, and the Pearson chi-squared or Fisher exact test to analyze categorical data. To control for possible confounding variables, linear models or linear regression will be applied for dependent continuous variables and logistic regression models for dependent categorical variables. Subgroup analysis of the primary outcomes will be stratified by participants’ sex. Analysis of variance will be used for the repeated measurement data. Analysis of the primary and secondary outcomes will be on an intention-to-treat (ITT) and a per-protocol (PP) basis. The result of the ITT analysis will be compared with that of the PP analysis to determine whether the results are consistent. Missing data will be handled according to the method of last observation carried forward. Adverse events will be listed and analyzed using the chi-square test or Fisher’s exact test.

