### Randomization and allocation concealment

Block randomization will be applied in this study. The participants will be divided into the “coma group”, “MCS group” or “VS group”, depending on their type of consciousness disorder. Each eligible participant will then be randomly assigned to either the intervention group or control group according to the 1:1 equal proportion rule. The sequence of random allocation will be generated using the PLAN function of the statistical software SPSS 24.0 (IBM,USA); this will be undertaken by an independent statistician from the Center of Evidence Based Medicine, NCU, who will not be involved in this trial. Also, the sequence of random allocation will be concealed to outcome assessors and the statistical analyst. The eligible participants’ allocation will also be concealed from their caregivers and from the therapists (including acupuncturist and cognitive therapists) after the participants’ baseline information has been assessed, and the therapists will be arrange the patients’ allocated treatments.

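### Allocation reads as blocked within coma, MCS and VS groups, but the outcome tests leave DOC type out unless a baseline test is significant, so the comparison is conservative and may lose power

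*Protocol article*

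**What the plan says.** On allocation, the section Randomization and allocation concealment states "Block randomization will be applied in this study" and continues: "The participants will be divided into the “coma group”, “MCS group” or “VS group”, depending on their type of consciousness disorder". The next sentence reads "Each eligible participant will then be randomly assigned to either the intervention group or control group according to the 1:1 equal proportion rule". The word stratified does not appear, but grouping first and allocating afterwards is most naturally read as blocks within each group.

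On analysis, the section Statistical analysis states: "For comparison of the primary or secondary outcomes between groups, the *t* test or non-parametric tests will be used to analyze continuous data". Categorical outcomes get a chi-squared or Fisher test. Covariates come in two ways: "A general linear model or logistic regression model will be applied to adjust for confounding influences if necessary", and, after baseline tests between the arms, "If statistical significance appears, the inequality factors will be treated as confounding variables in the final efficacy analysis". DOC type is not named as a covariate, a stratification term or a subgroup. The one subgroup factor named is sex.

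The primary outcome is the five-level GOS, and one of its levels is the vegetative state (section Primary outcomes).

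**The concern.** When allocation is balanced within a prognostic factor, the treatment estimate no longer varies because of that factor. A test that omits the factor still counts its spread as noise. The reported standard error is then too large, the true type I error falls below the nominal level, and power is lost.

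The protocol's adjustment rule does not repair this. It selects covariates by observed imbalance, not by prognostic value, so the factor that the design balances is the one least likely to be selected.

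DOC type is plausibly prognostic here. A VS patient enters at a condition that is itself a level of the primary scale, and the entry criteria set different minimum durations for coma (over one week) and for VS/MCS (over one month). What is at stake is a real effect being missed in a trial of 80.

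**Working it through.** **Inputs from the protocol (section Sample size):** difference δ = 2.01 GCS points, SDs 2.51 (active) and 1.90 (sham), α = 0.05, power 90%, 33 per group before dropout.

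**Assumptions:** R², the share of within-arm outcome variance explained by DOC type, from 0 to 0.5; three equal strata; permuted blocks of 4 within stratum. None of these is given in the protocol.

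**1. The protocol's own figure.** n = 2(1.960 + 1.282)² × 2.51² / 2.01² = 2 × 10.51 × 6.300 / 4.040 ≈ 32.8, so 33 per group. The stated figure is reproduced with a two-sided α and SD 2.51.

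**2. Standard error.** Unadjusted, the test reports SE = 2.51 × √(2/33) = 0.618. Under stratified allocation the true SD of the estimate is 0.618 × √(1 − R²). The reported SE is therefore too large by 1/√(1 − R²): 1.00, 1.05, 1.20 and 1.41 for R² = 0, 0.1, 0.3 and 0.5. At R² = 0.3 the true value is 0.618 × √0.7 = 0.517. Simulation gave a mean reported SE of 0.620 against an actual SD of 0.518.

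**3. Type I error and power at 33 per arm** (6,000 simulated trials per setting; t test v linear model with DOC type):

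| R² | Type I error, unadjusted | Type I error, adjusted | Power at 2.01, unadjusted | Power at 2.01, adjusted |
|---|---|---|---|---|
| 0 | 4.2% | 4.3% | 89.6% | 89.5% |
| 0.1 | 4.0% | 4.8% | 90.4% | 92.2% |
| 0.3 | 2.1% | 4.5% | 92.6% | 96.8% |
| 0.5 | 0.6% | 5.5% | 95.1% | 99.4% |

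At R² = 0 both tests are nominally 5%; the 4.2% and 4.3% are simulation results. If all 80 patients are evaluable, the R² = 0.3 powers are 96.8% v 98.7%. For a smaller effect of 1.5 points, which is not a protocol figure, power at 33 per arm is about 67% v 71% at R² = 0.1 and 69% v 82% at R² = 0.3.

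**4. The baseline trigger.** With blocks of 4 inside each stratum, a chi-squared test of DOC type by arm was significant in 0 of 6,000 trials in every setting.

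**5. Ordinal outcome.** This used five levels, 22 patients per stratum, an assumed log odds ratio of 1.4 (odds ratio e^1.4 ≈ 4.1), and an assumed gap between adjacent strata (5,000 trials per setting):

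| Gap (logits) | Null rejection, Mann–Whitney | Null rejection, van Elteren | Power, Mann–Whitney | Power, van Elteren |
|---|---|---|---|---|
| 0 | 5.1% | 5.3% | 87.8% | 87.2% |
| 0.5 | 4.9% | 5.3% | 85.3% | 86.2% |
| 1 | 3.2% | 4.8% | 81.4% | 86.6% |
| 2 | 0.9% | 4.8% | 59.1% | 84.2% |

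The loss is negligible up to 0.5 logits, about 5 points at 1 logit and about 25 points at 2 logits.

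**The case against.** **On the trial's own inputs the loss is modest.** At 2.01 points the unadjusted test keeps roughly the planned 90% at every R² examined, and adjustment adds 0 to about 4 points. This stands. A reader might infer a loss of 12 points or more, but on the GCS scale that needs an effect nearer 1.5 points together with an R² of 0.3 or above, and neither figure is in the documents. Large GOS losses likewise need strata that differ strongly. One assumed set of distributions, with MCS mostly in severe disability and coma and VS mostly in vegetative state, gave 45% v 64% at an odds ratio of 3 with 40 per arm. That is one point in an undocumented range.

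**Stratified allocation is inferred.** The Blinding section has envelopes issued in order of inclusion, which could describe a single sequence. Under one blocked sequence, simulation puts the unadjusted type I error at 4.6% to 5.2%, and the trigger fires in about 4% to 5% of trials. This stands as a caveat: the conservatism depends on the natural reading being right. The case for adjustment does not, because under a single sequence the unadjusted test simply keeps its SE of 0.618 and about 90% power, while adjustment would still reduce the residual variance.

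**Other planned methods might help.** The section also mentions linear models for confounders and analysis of variance for repeated measurements, and a within-patient contrast would remove stable differences between DOC types. But no covariate is named, and the repeated-measures analysis is not designated as the primary comparison. Data collection and management refers to a predetermined analysis plan, which may say more. The protocol nonetheless states the unadjusted tests and the significance rule outright, so this is more than detail left for later.

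**The sex subgroup.** A reader might infer that choosing sex widens the error bars. It does not. An interaction with DOC type would also be weak, with about 27 patients per class (80/3) if the classes are equal, so leaving it out is not an error.

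**Conclusion.** The point holds at the level of should fix. On the natural reading, the trial randomises within DOC type but does not analyse by it, and its adjustment rule cannot be expected to correct that. If DOC type is prognostic, the consequence is a conservative test and some lost power. There is no bias and no false-positive inflation, and the documents do not support calling it a fatal flaw.

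At the protocol's design effect on GCS, a secondary outcome, the cost is nil to about 4 points of power. It could be much larger for the primary GOS, but only if the strata differ by well over 1 logit. All sizes rest on assumed prognostic strength, equal strata and blocks of 4; with no prognostic value there is no loss.

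**What to change.** Name DOC type (coma, MCS, VS) as a pre-specified stratification term in the primary GOS analysis, using either a proportional-odds model with treatment and DOC type or a van Elteren test. Include it in the secondary-outcome models too. Apply it whatever the baseline tests show, and drop the significance-based trigger for this factor. With the proportional-odds model, report the odds ratio as conditional on DOC type; the gain there appears as power, not as a smaller standard error of the log odds ratio.

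State explicitly whether blocks are generated within DOC type, and reconcile this with the envelope order in the Blinding section.

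Separately and optionally, add a treatment-by-DOC-type interaction labelled exploratory. The Discussion part of the Abstract notes that existing reports mainly concern MCS, which gives a reason to look.

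The cost is wording only. DOC type is known for every patient before allocation, and no new data or patients are needed.
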